#### Data Management

The research study data manager will guide the data management responsibilities for this study. This study’s quantitative data will be collected using both paper and electronic case report forms, whereas qualitative data will be collected using audio recorders. Transcripts and field notes from the qualitative work as well as the paper case report forms will be kept under lock and key and will be overseen by the principal investigators. The transfer of participant-related data, if any, will be carried out in pseudonymized form; third parties will not have access to original data. REDCap (Research Electronic Data Capture; Vanderbilt University) will be used to enter, store, and manage quantitative data. To ensure that quality data are collected, the REDCap platform will provide an interface for data entry (an audit trail to track all changes within the database). In addition, automated validation checks will be embedded within the study database. The study data manager will share data queries generated from the accruing data with the research team on a biweekly basis.

### Data Analysis

#### Qualitative Data Analysis

Data generated from the qualitative interviews will be transcribed verbatim and analyzed using NVivo software version 14 (Lumivero) following a five-step framework approach: (1) *familiarization with the data*, (2) *identifying a thematic framework*, (3) *indexing*, (4) *charting*, and (5) *mapping and interpretation* [54]. This will help us generate an understanding of stakeholders’ experiences with the prototype. After the completion of the intervention prototype, a detailed analysis plan for this study will be developed. To adapt and inform our design and implementation processes, we will conduct systematic debriefings after each day of qualitative data collection. In weekly team meetings, we will share the first findings from these debriefings with all team members to adjust platform features to end users’ needs and facilitate implementation steps within the community.

#### Quantitative Data Analysis

We will summarize participant demographic characteristics and assess baseline balance between those randomized to the top-up and subscription arms. We will then assess the effect of offering the subscription model on the number of clinic visits with medication pickups (the main outcome) by comparing differences between those *offered* (including those who were offered and did not take up) the subscription model and those *offered* the top-up contribution model. As not all individuals will take up the offer, this will represent the intention-to-treat effect. We will estimate this effect using Poisson regression models. Next, we will assess the effect of the amount of money an individual contributed on the number of visits they attend. We will do this using a Poisson instrumental variable regression approach, where we use the random assignment as an instrument for the amount of money contributed. Finally, we will assess the effect of the random assignment to the different contribution arms on the proportion of individuals who take up the contribution model (the implementation outcome) using linear probability models and the effect on systolic and diastolic blood pressure readings using linear regression models.

#### Statistical Analysis

The baseline characteristics of participants will be compared between the 2 arms using medians and IQRs for continuous variables and proportions for categorical variables. Outcomes will be analyzed by both the intention-to-treat and per-protocol analysis methods using mixed effects Poisson regression methods for the primary outcomes. We will adjust for baseline imbalances for both the primary and secondary analyses, and both unadjusted and adjusted analyses will be presented. All our regression models will additionally control for baseline patient characteristics such as age, sex, and income to increase the precision of the treatment effects. We will not only conduct a complete case analysis but also present the results using multiple imputation as sensitivity analyses. Missing data on outcomes and key covariates will be assessed before analyses. Where applicable (missingness >10%), we will implement multiple imputation methods appropriate for random effects models. Two-tailed *P* values of ≤.05 will be considered to indicate statistical significance. Analysis will be performed with Stata software (version 17; StataCorp LLC). We will not conduct any interim analysis for this study.

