## Methods

### Study Setting

This design research study will take place in rural Nakaseke district, Uganda, with a population of 29,400 [31] (Figure 1). Nakaseke administratively belongs to the central region of Uganda, where an estimated 28.5% of the population are hypertensive [6]. Our study will focus on clients within Semuto Health Center IV, chosen during an early formative phase of research because the center has initiated an alternative, promising approach to manage blood pressure, which is described in the following subsection.

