#### Sample Size Estimation

On the basis of the range of recruited participants, we estimate the following minimal detectable effects (Table 5). For these calculations, our primary outcome is the number of clinic visits for medication pickups. On the basis of the 6-month study duration, this can range from 0 to 5 visits (individuals are asked to come once a month), which we will analyze as a count variable using Poisson regression. We additionally set an α of 5% and a power of 80%, with a 2-tailed *t* test for all estimates, and show the minimal detectable effects across a range of possible control counts (the number of visits for pickups among the voluntary contribution group in a range from 1 to 5) and sample sizes (ranging between 200 and 350). The minimum detectable effect is expressed as a rate ratio and measures the percentage increase in mean visits for the subscription contribution (intervention 1) compared with those for the voluntary contribution (intervention 2) over the 6-month study period.

**Table 5 table5:** Minimum detectable effect size across sample sizes and base rates.

Mean number of visits in the voluntary contribution (intervention 2) group	Minimum detectable effect size			
	200^a^	250^a^	300^a^	350^a^
1	1.44	1.39	1.35	1.32
2	1.30	1.27	1.24	1.22
3	1.24	1.22	1.20	1.18
4	1.21	1.19	1.17	1.16
5	1.19	1.16	1.15	1.14

^a^Total sample size (50% intervention 1 and 50% intervention 2).

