#### Randomization

Participants will be randomized to be offered either the subscription model or the top-up contribution payment model and assigned to the different models by study team members after the initial recruitment at the facility and upon providing informed consent. The allocation sequence for the random assignment of the intervention was developed by an independent statistician. Individuals are randomly assigned in a 1:1 ratio. We use stratified randomization by sex and day of recruitment, with participants randomized in blocks of 4 to maximize balance between treatment and control. The allocation is concealed because assignment is based on a random draw from a box such that an individual’s assignment is only revealed after they physically draw a slip.

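### The primary visit count is assigned Poisson regression in two sections and mixed effects Poisson, with no grouping factor named, in a third; the primary test is not fixed and can depend on which section is followed

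*Protocol article*

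**What the plan says.** All references are to the protocol article.

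- **Sample Size Estimation.** The primary outcome is the number of clinic visits for medication pickups, a total between 0 and 5 per client over six months, "which we will analyze as a count variable using Poisson regression". Table 5 gives minimum detectable rate ratios for it.
- **Quantitative Data Analysis.** For the intention-to-treat effect on the same outcome: "We will estimate this effect using Poisson regression models".
- **Statistical Analysis.** Outcomes are analysed "using mixed effects Poisson regression methods for the primary outcomes". If more than 10% of data are missing, "we will implement multiple imputation methods appropriate for random effects models". Significance is declared at a two-tailed P value of .05 or less.
- **Design.** "Our study will focus on clients within Semuto Health Center IV" (Study Setting). "Individuals are randomly assigned in a 1:1 ratio", and "We use stratified randomization by sex and day of recruitment" (both Randomization), in blocks of 4.

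No section says what the random effect is attached to.

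**The concern.** A random effect needs a grouping level. This trial has one facility, individual allocation and, as the sample size section describes it, one total per client. There is no site level and no repeated primary measure.

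Three candidates remain:

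- an intercept per client, which acts as an overdispersion term;
- monthly records nested in clients, which changes the form of the outcome;
- day of recruitment, which is a randomisation stratifier.

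Each differs from the model that the other two sections and Table 5 describe.

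The primary test therefore has two stated versions. Where their standard errors differ, so do the error rate, the power and possibly the verdict at .05. The trial is unblinded once the program starts, so the choice should be settled before outcome data are seen. This point is separate from the question of how well a Poisson model suits a count capped at 5.

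**Working it through.** **1. Which model lies behind Table 5?** Inputs from Sample Size Estimation: two-sided α of 5%, power of 80%, total N of 200 to 350 split equally, control means μ of 1 to 5. With n per arm, a Wald test on the log rate ratio and no extra-variance term:

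ln(RR) = (1.960 + 0.842) × √[(1 + 1/RR)/(nμ)]

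For N = 300 and μ = 2, RR = 1.243 solves this: 2.802 × √(1.8045/300) = 0.217 = ln(1.243). Table 5 gives 1.24.

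| Mean | N=200 | N=250 | N=300 | N=350 |
|---|---|---|---|---|
| 1 | 1.440 | 1.389 | 1.352 | 1.324 |
| 2 | 1.301 | 1.267 | 1.243 | 1.224 |
| 3 | 1.243 | 1.216 | 1.196 | 1.181 |
| 4 | 1.208 | 1.185 | 1.169 | 1.156 |
| 5 | 1.185 | 1.165 | 1.150 | 1.139 |

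Every cell is within 0.005 of the printed value (the largest gap is 1.165 against 1.16). Table 5 rests on variance equal to the mean, with no random effect.

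**2. When does the model-based standard error fail?** The documents give no distribution of attendance, so one is assumed: beta-binomial out of 5 visits, with p = μ/5 and within-client correlation ρ. Then

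φ = variance/mean = (1 − p)(1 + 4ρ)

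false-positive rate without a random effect ≈ 2[1 − Φ(1.96/√φ)]

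At μ = 2 (p = 0.4):

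| ρ | φ | False-positive rate |
|---|---|---|
| 0.1 | 0.6 × 1.4 = 0.84 | 3% |
| 0.3 | 0.6 × 2.2 = 1.32 | 9% |
| 0.5 | 0.6 × 3.0 = 1.80 | 14% |
| 0.7 | 0.6 × 3.8 = 2.28 | 19% |

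φ exceeds 1 only when ρ is above (1/0.6 − 1)/4 = 0.17 at mean 2, or above (1/0.4 − 1)/4 = 0.375 at mean 3.

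**3. If the random effect is a client intercept.** Simulation with no arm effect, 150 per arm, mean 2. Entries are false-positive rates in two separate runs (600 / 400 replicates):

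| ρ | Poisson, model-based SE | Poisson, client intercept |
|---|---|---|
| 0.3 | 9% / 8% | 5% / 5% |
| 0.5 | 12% / 14% | 5% / 4% |
| 0.7 | 19% / 22% | 4% / 6% |

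At ρ = 0.5 the standard errors were 0.082 and 0.123. At ρ = 0.1 the two models agreed. Poisson with robust standard errors gave 4.5–5.7% over all scenarios of the first run and 4–6.5% in the second. A further run over ρ of 0.3–0.7 gave about 11–17% without a random effect, against about 4–8% with robust errors or a client intercept.

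With a true effect and ρ = 0.4 (150 replicates each):

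- Mean 1, RR 1.35: power 72% without and 48% with the intercept; verdicts differed in 24% of trials.
- Mean 2, RR 1.24: power 76% and 63%; verdicts differed in 13%.

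Every disagreement had the model without a random effect significant and the mixed model not. With variance/mean at or below 1 there were no disagreements.

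**4. One data set, two verdicts.** Constructed counts of 0/1/2/3/4/5 visits, 150 per arm: 55/25/20/15/15/20 and 45/22/20/17/19/27. Totals are 270 and 324, means 1.80 and 2.16, variance/mean 1.84 and 1.66.

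- No random effect: log RR = ln(2.16/1.80) = 0.182; SE = √(1/270 + 1/324) = 0.082; p = 0.027.
- Client intercept: log RR 0.200, SE 0.120, p = 0.094.
- Robust SE: √(1.84/270 + 1.66/324) = 0.109; z = 0.182/0.109 = 1.67; p about 0.095.

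**5. If the random effect is day of recruitment.** Same null scenario with 15 or 25 recruitment days (assumed), arms balanced within day and no between-day variation. The SE was 0.082 in both models and the verdicts never differed. Both had false-positive rates of about 8–9%, 14–15% and 20–21% at ρ of 0.3, 0.5 and 0.7.

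**6. Effect on Table 5.** Multiplying the variance in step 1 by φ (taken as equal in both arms), at N = 300 and mean 2: RR rises from 1.24 to 1.28 (φ = 1.32), 1.33 (φ = 1.80) or 1.38 (φ = 2.28).

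**The case against.** Mixed effects Poisson is itself a form of Poisson regression, and no section says that random effects are excluded. The Statistical Analysis section can be read as the specific statement and the other two as outlines; a simpler planning model for sample size is common. The grouping factor could be named in a fuller document that is not shown. Table 4 lists clinic visits as well as medication pickups as primary, and the Statistical Analysis section uses the plural for primary outcomes, so a single count is not beyond dispute. Where the mixed model has a client intercept it controls error acceptably, so naming the grouping factor would also resolve the conflict.

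Much of this stands. It shows that the wording can be harmonised in either direction. It does not remove the problem: as written, a reader cannot tell which test is primary, and the general-to-specific reading still leaves the random effect undefined and Table 5 computed without one. The two sections that describe the main outcome most closely both treat it as a single count.

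A reader might also infer that the design contains no cluster at all, so that the random effect must be a client intercept or monthly records and the two versions must diverge. The documents do not support that. Day of recruitment is a grouping within the randomisation, and step 5 shows that under that reading the two versions can coincide.

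**Conclusion.** The inconsistency is real and concerns the primary analysis. Its consequence is conditional on two things that the documents do not give: what the random effect is, and how much attendance varies between clients.

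- **Client intercept, overdispersed counts** (ρ of about 0.3 or more at mean 2): false-positive rate about 9–19% without the random effect against about 5% with it, and verdicts can differ on the same data.
- **Day of recruitment, no between-day variation:** the versions agree, but both carry the inflated error. Between-day variation was not examined.
- **Low correlation** (0.1 at mean 2, or variance/mean at or below 1 generally): no inflation and no disagreement.
- **Repeated monthly records:** a different form of the outcome, not sized here.

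Overdispersion is plausible, because contribution is voluntary and clients who decline the offer stay in the analysis, but it is not established. It would go too far to say that the planned test is known to be anti-conservative or that the trial's result will depend on the model. The simulations are modest, with Monte Carlo error of roughly 1 to 4 percentage points.

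**What to change.** 1. State one primary model in Sample Size Estimation, Quantitative Data Analysis and Statistical Analysis: Poisson regression on the per-client visit count with robust (sandwich) standard errors. When attendance is heterogeneous, this protects the error rate whichever random effect was meant.
2. In Statistical Analysis, delete *mixed effects* from the primary-outcome sentence and the clause tying the imputation to random effects models.
3. Add a note under Table 5 that its rate ratios assume variance equal to the mean and would be larger if attendance is overdispersed (for example 1.28 to 1.38 in place of 1.24 at N = 300 and mean 2, for variance/mean of 1.32 to 2.28).

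If a mixed model is intended, the alternative is to name its grouping factor and bring Sample Size Estimation, Quantitative Data Analysis and Table 5 into line with it.

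The cost is a few sentences, one Stata option and a table note. The statistical price is a wider confidence interval and less favourable detectable effects if attendance proves heterogeneous.

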Primary outcome	Number of NCD^a^ clinic visits as well as number of medication pickups	Health facility records
Implementation and medication outcomes	Percentage of people who take up funding models Total amount contributed to the clinic funds	Directly from MoPuleesa platform
Long-term health outcome	Systolic and diastolic blood pressure readings	Collected through CHWs^b^ and health facility records
User experience outcome	User satisfaction	Questions on user satisfaction in baseline and follow-up surveys

^a^NCD: noncommunicable disease.

^b^CHW: community health worker.

Participants will be asked to fill out a questionnaire at baseline and after 6 months that will address care-seeking behavior, the consistency of medication pickups, health-related money-saving routines, and the perceptions of care quality. At baseline, the questionnaire will also include sociodemographic characteristics. At 6 months, the questionnaire will further include questions about the feasibility and acceptability of the intervention, as well as a short series of platform attribute or Kano-style questions (the Kano model describes the relationship between product attributes and user satisfaction or disapproval to determine the relative importance of product features [44]). In addition, we will use data routinely collected at clinic level (demographic data, blood pressure readings, and height and weight measurements) and via the MoPuleesa prototype (money contributed and medication ordered) as detailed in Table 4.

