#### Quantitative Component

For the quantitative component, we anticipate enrolling between 200 and 350 clients. Client recruitment will follow the same procedures as those outlined in the previous subsection. This number was not the result of a detailed power calculation; rather, it was determined and constrained by the total client population from which we can recruit. Specifically, based on our discussion with the administrators of the NCD study clinic at Semuto Health Center IV, the clinic currently serves approximately 380 clients who meet the aforementioned inclusion criteria. Thus, we realistically expect to enroll 200 to 350 clients based on exact attendance during the study period and refusal rates.

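### Covariate adjustment is triggered by observed baseline imbalance, no primary model is fixed, and recruitment day and baseline outcome values are not named

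*Protocol article*

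**What the plan says.** The Quantitative Data Analysis section has the team check balance between the arms first and estimate the effect afterwards. The Statistical Analysis section then sets two rules for covariates. The first is triggered by imbalance: "We will adjust for baseline imbalances for both the primary and secondary analyses, and both unadjusted and adjusted analyses will be presented". The second is a standing rule that applies whatever the balance check shows, and its stated purpose is precision: "All our regression models will additionally control for baseline patient characteristics such as age, sex, and income".

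The same section calls the primary model a mixed effects Poisson regression without naming the random effect. The Sample Size Estimation and Quantitative Data Analysis sections mention only Poisson regression.

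The Randomization section says: "We use stratified randomization by sex and day of recruitment". Under Main Hypothesis, the baseline questionnaire covers "care-seeking behavior, the consistency of medication pickups", and blood pressure comes from routine clinic data. The planned blood pressure analysis is "the effect on systolic and diastolic blood pressure readings using linear regression models", with no mention of a baseline reading.

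**The concern.** In a randomized trial, a baseline difference between arms is chance, and the test already allows for it. Covariates earn a place by predicting the outcome, and they should be fixed before the data are seen. A rule that looks at balance first and then decides what to adjust for makes the primary model a function of the data. With no threshold, two analysts could follow the text and fit different models.

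Two estimates are promised and neither is primary, so the choice of headline result stays open. The Blinding section states that neither the team nor the participants are blinded once the program starts. Prespecification is therefore one of the few safeguards available.

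Precision is also scarce. The Quantitative Component section puts the eligible clinic population at approximately 380, so it cannot be bought by enrolling many more clients. The variables most directly related to the outcomes are collected, but the covariate sentence does not name them.

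**Working it through.** **1. Design against analysis.**

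| Item | Stated elsewhere in the article | Named as a covariate |
|---|---|---|
| Sex | stratification factor | yes |
| Recruitment day | stratification factor | no |
| Pickup consistency | baseline questionnaire | no |
| Blood pressure | routine clinic data | no |
| Definition of an imbalance | none given | – |
| Primary result: adjusted or unadjusted | none given | – |

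**2. Reproduce Table 5.** Inputs: "We additionally set an α of 5% and a power of 80%, with a 2-tailed" test (Sample Size Estimation); "Individuals are randomly assigned in a 1:1 ratio" (Randomization); "we anticipate enrolling between 200 and 350 clients" (Quantitative Component). With control mean m, rate ratio R and n = N/2 per arm, solve

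ln R = (1.960 + 0.842) × √[(1/m + 1/(mR))/n].

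For m = 3 this gives 1.243, 1.216, 1.196 and 1.181 at N = 200, 250, 300 and 350. Table 5 has 1.24, 1.22, 1.20 and 1.18. All 20 cells agree to within about 0.005. Table 5 is therefore an unadjusted calculation with pure Poisson variance, and no figure in it is wrong.

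**3. What adjustment can do for the primary outcome.** Let φ be the squared coefficient of variation of clients' underlying rates (extra-Poisson variation). The bracket becomes (1/m + 1/(mR) + 2φ)/n. Assume φ = 0.25 with m = 3 and N = 200:

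- covariates explain none of it (φ stays 0.25): R = 1.338
- covariates explain half (φ = 0.125): R = 1.293
- covariates explain all (φ = 0): R = 1.243, the Table 5 value

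The best case is Table 5 itself. If φ = 0 at the outset, there is nothing to gain.

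This illustration, like Table 5, ignores the cap of 5 visits. In the first case the subscription mean would be 3 × 1.338 = 4.01. The assumed variance there is 4.01 + 0.25 × 4.01² = 8.0, but a count between 0 and 5 with that mean cannot exceed 4.01 × (5 − 4.01) = 4.0. The m = 3 figures show direction only. At m = 2 and N = 200 the same φ stays within the cap and moves R from 1.301 to 1.387.

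**4. Blood pressure.** In a linear model, adjusting for a baseline reading with correlation ρ multiplies the detectable difference by √(1 − ρ²). Assumed ρ = 0.3, 0.5 and 0.7 give 0.954, 0.866 and 0.714.

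**5. Illustrative null simulation.** All effects are assumed: N = 270, 18 recruitment days, log-scale day SD 0.3, baseline covariate coefficient 0.35, robust standard errors, 1,500 runs.

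| Analysis | Mean SE of log rate ratio | Rejection at 5% |
|---|---|---|
| Unadjusted | 0.094 | 4.3% |
| Sex plus two weak covariates | 0.093 | 4.3% |
| The same, plus imbalance-triggered covariates | – | 3.7% |
| Better of unadjusted and imbalance-triggered | – | 5.1% |
| Sex and weak covariates, plus baseline covariate and day dummies | 0.070 | 6.8% |

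Naming prognostic covariates helps under these assumptions. Many small day strata fitted as fixed effects carry a cost of their own.

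**The case against.** The strongest reply is that this is a condensed article. Its covariate list is introduced as examples, its mixed model has an unnamed random effect that could be recruitment day, and an analysis plan not shown may close the list. That stands in part. A reader might infer that day and baseline outcome values are left out of the models, but the document supports only that they are not named. It does not excuse the imbalance rule or the missing primary estimate, because the first is a stated method and an analysis plan faithful to this text would inherit it.

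Other stronger readings also fail:

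- **Better detectable effects than Table 5.** A reader might scale ln(1.30) by √(1 − r²) and take 1.30 down to 1.28, 1.26 or 1.23 for r = 0.3, 0.5 or 0.6. That formula belongs to linear models. In a simulated check at mean 2 and N = 200, with covariate-outcome correlations of about 0.39 and 0.56, the adjusted standard error stayed near 0.10. That is the Table 5 value, √[(1/2 + 1/2)/100]. The unadjusted robust standard error rose to about 0.11 and 0.125.
- **Inflated type I error.** The illustration gave 5.1% even when the better of two results was picked. The harm is lost prespecification, not a demonstrated error rate.
- **Large day effects.** Nothing in the article links recruitment day to later pickups.
- **A flat contradiction between all models being adjusted and unadjusted results being shown.** Unadjusted may mean without the imbalance terms only. The wording is ambiguous.
- **Missing covariates ignored.** The section plans to assess missingness in key covariates and to use multiple imputation as a sensitivity analysis above 10%. Its complete-case analysis would still drop clients who lack, for example, income.
- **A baseline visit count exists.** For the primary outcome, the documented baseline measure is a questionnaire item on pickup consistency.

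**Conclusion.** The point holds as a poorly fixed method. The protocol lets observed imbalance choose covariates, gives no threshold or closed list, and names no primary estimate. It also does not carry recruitment day or a baseline outcome value into the named covariates, though it may intend to.

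The gain on the primary outcome cannot be sized, because no correlation, day effect or overdispersion is given. Within Table 5's Poisson framework, adjustment protects the stated detectable effects and does not better them. At assumed φ = 0.25, mean 3 and N = 200, the range is 1.34 with nothing explained to 1.24 with everything explained, subject to the cap noted above. For blood pressure, the detectable difference would shrink by about 5%, 13% or 29% at assumed correlations of 0.3, 0.5 or 0.7. The change should be made, but nothing here invalidates the trial.

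**What to change.** 1. Delete the sentence that ties adjustment to baseline imbalance. Keep the baseline table as description.
2. Prespecify one primary model: arm, sex, recruitment day as a random intercept, age, and the baseline questionnaire measure of pickup consistency. A random intercept is preferable to many day dummies. If income is wanted, name it now.
3. Analyse systolic and diastolic pressure by ANCOVA, each with the baseline reading of the same measure, and state which clinic reading counts as baseline.
4. Label the unadjusted estimate supportive, and reword the sentence about all models so that the two fit together.
5. State how clients with missing baseline covariates stay in the primary model, not only in the sensitivity analysis.

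The cost is analysis wording, settled before outcome data are examined. The article already lists the variables as collected or recorded, so no new data collection is needed.

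### The main adjusted intention-to-treat estimate drops randomised clients whose visit count is known when a baseline item such as income is blank

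*Protocol article*

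**What the plan says.** Four statements in the Statistical Analysis section bear on this.

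- Covariates: "All our regression models will additionally control for baseline patient characteristics such as age, sex, and income to increase the precision of the treatment effects".
- Presentation: "both unadjusted and adjusted analyses will be presented".
- Base analysis: "We will not only conduct a complete case analysis but also present the results using multiple imputation as sensitivity analyses".
- Threshold: "Where applicable (missingness >10%), we will implement multiple imputation methods appropriate for random effects models".

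The Quantitative Data Analysis section defines the intention-to-treat effect by the model a client was offered. Refusers are counted in their arm: "including those who were offered and did not take up) the subscription model". Table 4 takes the primary outcome, visits and medication pickups, from health facility records. The sociodemographic items have a different source, the survey: "At baseline, the questionnaire will also include sociodemographic characteristics". The Sample Size Estimation section puts the visit count on a scale from 0 to 5.

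**The concern.** The outcome and the covariates come from different sources. A client can have a complete visit record and an incomplete questionnaire. A regression on complete cases that contains income removes that client, although nothing about the outcome is unknown. At or below 10% missing, no planned adjusted analysis brings the client back. Above 10%, only a sensitivity analysis does, so the main adjusted estimate rests on a reduced set in both situations.

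This does not fit the plan's own intention-to-treat definition, which covers everyone offered either model. It also works against the stated purpose of adjusting, which is precision, because deleting clients gives some precision back. In a trial of payment models, income is also the covariate for which non-response is least comfortable to ignore.

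**Working it through.** **Inputs.** Two-sided alpha 5%, power 80%, total N from 200 to 350, control means from 1 to 5 and a Poisson count (Sample Size Estimation, Table 5); 1:1 allocation (Randomization). The protocol states no rate of blank baseline items. I assume that a share q of clients, 5% to 10%, has at least one.

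**Step 1: reproduce Table 5.** With n = N/2 per arm, control mean m and rate ratio RR, solve

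ln(RR) = (1.960 + 0.842) × √[(1/m + 1/(m·RR))/n].

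For m = 3 and N = 200, RR = 1.243: the right side is 2.802 × √[(0.3333 + 0.2682)/100] = 0.217, and ln(1.243) = 0.218. Table 5 prints 1.24. For m = 1, N = 200 the result is 1.440 (printed 1.44); for m = 3, N = 350 it is 1.181 (printed 1.18). All 20 cells agree to within about 0.005, which is rounding. Table 5 thus counts every enrolled client and allows no loss for blank covariates.

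**Step 2: clients lost.** The number dropped is q × N.

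- q = 10%: 20 of 200, or 35 of 350.
- q = 5%: 10 of 200, or about 18 of 350.

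**Step 3: power at the Table 5 effects.** Power = Φ(2.802 × √(1 − q) − 1.960).

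- q = 0: Φ(0.842) = 80%.
- q = 5%: Φ(2.731 − 1.960) = Φ(0.771) = 78.0%.
- q = 10%: Φ(2.658 − 1.960) = Φ(0.698) = 75.7%.

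**Step 4: detectable ratio after the loss.** Replace N by N(1 − q) in Step 1.

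| Control mean, N | No loss | 5% lost | 10% lost |
|---|---|---|---|
| 1, 200 | 1.440 | 1.453 | 1.467 |
| 3, 200 | 1.243 | 1.249 | 1.257 |
| 3, 350 | 1.181 | 1.186 | 1.191 |

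These figures give no credit for the precision that adjustment may add. They show the cost of deletion alone.

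**Step 5: with the blanks filled.** Every randomised client with a recorded count stays in, so q = 0 and the Table 5 figures stand.

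**The case against.** The strongest reply is that the unadjusted analysis is also presented. It needs only arm and visit count, keeps these clients, and is the comparison that Table 5 describes. This stands: the trial would not be without an intention-to-treat estimate on the full set. It does not settle the matter, because the next sentence puts covariates in all regression models and the protocol does not say which result leads.

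Second, few of the named covariates can be blank. Sex is a stratification factor. Age is needed to confirm eligibility, and demographic data are also collected routinely at the clinic. That leaves mainly income. REDCap validation checks and biweekly data queries should also limit blanks. This stands too, and it bounds the size. A reader might multiply several covariates: three, each 10% blank independently, would lose 1 − 0.9³ = 27.1% of clients and bring power to about 67%. The documents do not support that as the expected case. The covariate list is open, but no further item is named and no rate is given.

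Third, no bias between arms is shown. If baseline items are recorded before the slip is drawn, which is plausible but not stated, their missingness cannot depend on arm, and the reduced set still gives a valid randomised comparison. A reader might infer that the estimate is distorted because clients who withhold income pay and attend differently. The protocol offers no evidence for that; it is a question of whom the estimate describes.

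Fourth, whether the 10% applies per variable or per client is detail that an analysis plan not shown here may settle. I do not count it as a fault.

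**Conclusion.** The point holds for the adjusted intention-to-treat models. The stated rule removes randomised clients with a known outcome because a questionnaire covariate, mainly income, is blank, and it does so below and above the 10% threshold. A reader might take the threshold to mean that imputation takes over once missingness passes 10%. The text does not say so, since imputed results remain a sensitivity analysis.

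The size is modest: with 5% to 10% of clients affected, two to four points of power and at most about 0.02 on the detectable ratio at a mean of 3 visits. If about 223 clients or more are enrolled, a 10% loss still leaves at least 200 (223 × 0.9 = 200.7), inside the range that Table 5 covers. The main reason to act is that the adjusted estimate should cover the set that the plan itself defines, and that this costs almost nothing. The size rests on the assumed missingness. The mechanism also assumes that income is collected in the baseline questionnaire; the article does not name it there, and the clinic data it lists do not mention it.

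**What to change.** In the Statistical Analysis section:

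- State that the adjusted intention-to-treat models include every randomised client with a recorded outcome. Fill blank baseline covariates at any level of missingness with the mean or mode taken over both arms together, plus a missing indicator.
- Drop the 10% threshold for baseline covariates. Reserve the complete-case and multiple-imputation comparison for outcomes that can truly be missing, namely blood pressure and survey items.
- State that no recorded visit counts as 0 for clients still under follow-up, and handle clients who withdraw consent separately. Scoring every absent record as 0 would turn withdrawals into non-attendance.
- Confirm that baseline items are recorded before the slip is drawn, since the argument for the fill depends on it.

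The cost is a few sentences, a few lines of code and one indicator term per incomplete covariate, with no new data. The justification comes from randomisation, so it applies to the intention-to-treat comparison and does not carry over to the planned per-protocol analysis, where missing covariates need their own treatment.
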